#### Data collection and management

2.3.3

Prior to formal testing, all participants will receive a system operation manual and familiarize themselves with the mini-program's interface and functions. To simulate real-world usage, no additional structured training will be provided. Participants will engage with the mini-program for 1 month, with technical support available upon request.

Data will be collected at two time points: baseline (T0, enrollment) and follow-up (T1, 1 month after initial use). At T0, demographic characteristics will be recorded, together with the validated 8-item eHealth Literacy Scale (eHEALS) (52). At T1, online surveys will be distributed via the Wenjuanxing platform (Version 3.0.10) to assess system usability (MAUQ) and self-reported task performance. Meanwhile, user interaction data will be automatically collected through the mini-program's backend, including function usage frequency, session duration, and time spent on each page. These metrics will be used to characterize actual engagement behaviors and interaction patterns. A purposive subsample of participants will also be invited to complete brief semi-structured interviews at T1. Interviews will be audio-recorded, transcribed verbatim, and organized for qualitative analysis.

All data will be independently entered and cross-checked by two researchers to ensure accuracy. Data collection and management will adhere to a predefined protocol, with personally identifiable information anonymized during storage and analysis. Access to data will be restricted to authorized research personnel.

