### Phase 3: evaluation

2.3

Upon completion of development, the mini-program will undergo a mixed-method usability evaluation. Quantitative measures will draw on the mHealth App Usability Questionnaire (MAUQ), demographic and eHealth literacy (eHEALS) questionnaires, backend interaction analytics, and structured task-based performance metrics. To complement these data, brief post-test interviews will be conducted to explore users' experiences, perceived barriers, and improvement suggestions. Insights derived from integrating performance metrics with user narratives will guide iterative refinements and ensure that the program meets the needs of patients, caregivers, and healthcare professionals. All usability testing procedures and outcomes will be documented in accordance with ISO/IEC 25062 (49) (Common Industry Format for Usability Test Reports) for standardized and comprehensive reporting.

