**(2) Secondary outcomes**

Task performance

As part of the usability evaluation, task performance will be assessed to objectively measure users' ability to navigate and interact with the mini-program. A set of representative tasks will be developed based on the system's core functionalities, simulating common usage scenarios. The evaluation will be conducted in accordance with the usability principles outlined in ISO 9241–11 (54). At the end of the trial, participants will be asked to independently complete these predefined tasks. The Task Completion Rate (TCR)—defined as the percentage of users who successfully complete the assigned tasks—will serve as a key usability metric. A TCR of ≥80% is generally considered indicative of good usability (55), though this threshold may vary depending on task complexity and context. Additionally, Task Completion Time (TCT) will be recorded to assess task efficiency, while the Error Rate (ER) will quantify operational inaccuracies. The Assistance Rate (AR)—indicating the level of external support needed—will be used to evaluate users' reliance on external guidance.

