## Discussion

3

The presented study protocol outlines a patient-centered WeChat-based digital health intervention for esophageal cancer patients, developed through Patient Journey Mapping (PJM) and informed by the Integrated Theory of Health Behavior Change (ITHBC).

Unlike previous mHealth interventions for cancer patients that often lack user engagement and contextual relevance (29, 57), this study incorporates PJM to systematically identify health management needs across the care continuum. This user-informed approach improves alignment with patient experiences and addresses critical gaps in existing care pathways, which may inform future refinement of digital health strategies and clinical services.

Furthermore, the mini-program has the potential to enhance patient self-management and optimize healthcare resource utilization. At the individual level, a disease-specific digital health tool may improve patients' disease awareness, strengthen self-management capabilities, and ultimately enhance their quality of life (58). Compared to previous mHealth studies, this program offers advantages in interactivity, allowing for a more personalized and adaptive user experience. At the system level, it could help reduce avoidable hospital visits and streamline care delivery, thereby potentially lowering medical costs.

Third, the mixed-method usability evaluation enhances the interpretability of findings. Quantitative metrics provide objective evidence of system performance, whereas post-test interviews help uncover contextual factors and latent user needs that cannot be captured by metrics alone. This integrated approach aligns with recommended practices for early-stage digital health evaluation and supports targeted, evidence-informed refinement of the mini-program.

This study integrates PJM and ITHBC to inform the development of a targeted digital health intervention. By grounding the design in patient needs and behavioral theory, the mini-program is expected to promote user engagement and adherence. Although tailored to EC patients, this methodological approach may provide a useful reference for developing digital health tools for other chronic disease populations.

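### Section 2.3.3 collects task performance by self-report in an online survey, while section 2.3.4 calls it an objective measurement on performed tasks; the source of TCR, TCT, ER and AR must be reconciled

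*Protocol article*

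**What the plan says.** Section 2.3.3 (Data collection and management, Phase 3) sets out what is gathered at T1, one month after first use. Surveys on the Wenjuanxing platform are sent out "to assess system usability (MAUQ) and self-reported task performance". The same section lists the backend data: how often functions are used, session length and time per page. It describes no observer, recording or log for a task session.

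Section 2.3.4 (2) (Secondary outcomes) describes a different procedure. There, "task performance will be assessed to objectively measure users' ability to navigate and interact with the mini-program". At the end of the trial, "participants will be asked to independently complete these predefined tasks". For the metrics, "Task Completion Time (TCT) will be recorded to assess task efficiency, while the Error Rate (ER) will quantify operational inaccuracies", and an assistance rate captures reliance on outside help. TCR is the percentage of users who complete the assigned tasks, with 80% or more given as a sign of good usability.

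Other places side with 2.3.4. Table 1 gives task-based testing its own row in Phase 3, apart from the MAUQ and the backend data. The opening of section 2.3 lists "backend interaction analytics, and structured task-based performance metrics" as separate quantitative measures.

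Section 2.3.5 (Statistical analysis) tests TCR against the benchmark with a one-sample proportion test and summarises TCT, ER and AR descriptively. It does not say which source feeds them.

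**The concern.** A team working from 2.3.3 and a team working from 2.3.4 would collect different data under the same outcome names. This goes beyond condensed detail, because the article states two incompatible modes of collection.

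The choice matters for three reasons. First, a participant who ended a task wrongly may believe it succeeded, and recalled times, error counts and requests for help are open to recall and desirability error. Second, self-report would come from the same respondent, platform and time point as the MAUQ, so the task metrics would no longer be the separate objective measure that 2.3.4 describes. Third, TCR is the only outcome tested against a benchmark, and failures reported as successes push that test in the favourable direction.

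**Working it through.** **Step 1: the text side by side.**

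| Place | Task performance is |
|---|---|
| 2.3.3 | self-reported, by online survey at T1 |
| 2.3.4 (2) | objectively measured on predefined tasks performed at the end of the trial, with time recorded |
| Table 1 | a testing activity on its own row |
| 2.3, opening | structured task-based metrics, listed apart from the MAUQ |

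Could the survey item be an extra measure beside an observed test? Section 2.3.4 lists no self-reported task outcome and 2.3.5 analyses none. The only task metrics are TCR, TCT, ER and AR, and the only source that 2.3.3 names for task performance is the survey. The backend variables it lists do not include task success, errors or assistance. So the text does not settle the matter.

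**Step 2: size, as an illustration only.** The protocol states no misreporting rate, so there is no figure of its own to reproduce.

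Inputs from the protocol:
- Benchmark 80% (2.3.4) and a one-sample proportion test (2.3.5).
- Target sample 34–40 (2.3.2). The minimum group sizes there add to 12 + 8 + 8 = 28, used as a lower case.

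Assumptions:
- Exact binomial test, one-sided 5% (level and sidedness are not stated in the article).
- True TCR p = 0.80, exactly at the benchmark.
- A share f of true failures is reported as success, and no success is reported as failure.
- One outcome per user, and all n users contribute.

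Expected reported rate: p' = p + (1 − p)·f.
- f = 0.10: 0.80 + 0.20 × 0.10 = 0.82
- f = 0.25: 0.80 + 0.20 × 0.25 = 0.85
- f = 0.50: 0.80 + 0.20 × 0.50 = 0.90

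Critical value: the smallest r with P(X ≥ r) ≤ 0.05 when X ~ Bin(n, 0.80). The chance of wrongly exceeding the benchmark is P(X ≥ r) when X ~ Bin(n, p').

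| n | r | f = 0 | f = 0.10 | f = 0.25 | f = 0.50 |
|---|---|---|---|---|---|
| 28 | 27 | 1.5% | 2.8% | 6.3% | 21.5% |
| 34 | 32 | 2.3% | 4.2% | 9.7% | 32.6% |
| 40 | 37 | 2.8% | 5.4% | 13.0% | 42.3% |

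The effect is small at f = 0.10 and becomes material from about f = 0.25. This covers TCR only; nothing in the article allows a similar calculation for TCT, ER or AR.

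**The case against.** The strongest reply is that the protocol's weight lies on one side. Self-report appears in a single phrase. Table 1, section 2.3 and section 2.3.4 all describe a performed test, and 2.3.3 itself opens by referring to formal testing. The phrase may be a stray adjective or an unlisted extra item, and who records times and errors is detail an article may leave to the full protocol. The primary outcome is a questionnaire by design and is untouched, and the study is exploratory.

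Most of this stands. It makes the survey reading the less likely one and limits the severity. It does not remove the contradiction, because 2.3.3 is the section that says how Phase 3 data are collected.

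A reader might infer that the four secondary outcomes are biased. The documents support only a risk of bias, and only if 2.3.3 is followed.

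A reader might also assume over-reporting of 10 to 15 percentage points and conclude that a poor TCR of 70% would pass as 80–85%. The documents give no basis for that amount, and the plan is a test, not a reading of the point estimate. Under the assumed exact test, exceeding 80% needs 32 of 34 or 37 of 40 successes (32/34 = 94%, 37/40 = 92.5%). An expected reported rate of 85% achieves that in only 9.7% to 13.0% of trials.

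Finally, the Discussion's line that "Quantitative metrics provide objective evidence of system performance" is weak evidence here. It covers all the quantitative measures, the MAUQ included, and does not say how task data are captured.

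**Conclusion.** The contradiction between 2.3.3 and 2.3.4 is real and reaches all four secondary metrics, including the one tested against a benchmark. Whether it leads to bias depends on which section is followed, and the protocol gives no size. On the assumptions set out above, with 34 to 40 users, the chance of wrongly exceeding 80% goes from about 2–3% to 4–5%, 10–13% or 33–42% as the share of misreported failures goes from none to 10%, 25% or 50%. Those shares are illustrative and not estimates. Severity is moderate: only secondary outcomes of an exploratory study are affected, but times, errors and assistance not captured during the session cannot be recovered afterwards.

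**What to change.** Reconcile 2.3.3 with 2.3.4 before Phase 3 starts:
- Remove self-report in the T1 survey as the source of the secondary outcomes.
- State that TCR, TCT, ER and AR are captured during the task-based testing already scheduled in Table 1, by existing study staff, screen recording or task-level event logs, against success criteria set in advance. Assistance is noted in the same session.
- Do not rely on the page-level time already collected. Alone it does not give completion, errors or assistance.
- If a self-rating of task performance is kept, label it supplementary and report it apart from the four metrics.

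The cost is a few sentences of corrected wording and a small set-up effort for capture. The session is already planned, and the Data Availability statement says that no data have yet been collected.

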#### Outcomes measures

2.3.4

**(1) Primary outcome**

mHealth App Usability Questionnaire

The usability of the mini-program will be assessed using the Chinese version of the mHealth App Usability Questionnaire (MAUQ). The MAUQ comprises 21 items across three dimensions: ease of use and satisfaction, system information arrangement, and usefulness. Each item is rated on a 7-point Likert scale (1 = strongly agree; 7 = strongly disagree). The overall usability score is calculated as the average of all item responses, with scores closer to 1 indicating better usability. The Chinese version has demonstrated good reliability and validity, with a total questionnaire Cronbach's α of 0.912 and dimension-specific Cronbach's α values of 0.912, 0.884, and 0.907, respectively (53).

**(2) Secondary outcomes**

Task performance

As part of the usability evaluation, task performance will be assessed to objectively measure users' ability to navigate and interact with the mini-program. A set of representative tasks will be developed based on the system's core functionalities, simulating common usage scenarios. The evaluation will be conducted in accordance with the usability principles outlined in ISO 9241–11 (54). At the end of the trial, participants will be asked to independently complete these predefined tasks. The Task Completion Rate (TCR)—defined as the percentage of users who successfully complete the assigned tasks—will serve as a key usability metric. A TCR of ≥80% is generally considered indicative of good usability (55), though this threshold may vary depending on task complexity and context. Additionally, Task Completion Time (TCT) will be recorded to assess task efficiency, while the Error Rate (ER) will quantify operational inaccuracies. The Assistance Rate (AR)—indicating the level of external support needed—will be used to evaluate users' reliance on external guidance.

**(3) Other measurements**

General information questionnaire

Demographic and clinical data will be collected using a custom-designed questionnaire developed by the research team. Demographic variables include age, sex, residence, employment status, education level, marital status, family monthly income per capita, primary caregiver, and medical expense payment method. Clinical variables include histological type of EC, tumor staging, and pathological classification.

eHealth literacy

eHealth literacy will be measured using the 8-item eHealth Literacy Scale (eHEALS), which evaluates individuals' perceived ability to seek, understand, and use electronic health information. Each item is rated on a 5-point Likert scale, with higher scores indicating better eHealth literacy. The eHEALS has been widely validated across diverse populations and consistently demonstrates good internal consistency and construct validity (56).

#### Statistical analysis

2.3.5

Data will be analyzed using IBM SPSS Statistics version 29.0 (IBM Corp.). The primary outcome, overall usability measured by the Chinese version of the mHealth App Usability Questionnaire (MAUQ), will be summarized using mean ± standard deviation (SD) and 95% confidence intervals (CI).

For secondary outcomes, the task completion rate (TCR, %) will be evaluated using a one-sample proportion test to assess whether it reaches the predefined usability benchmark. Other task performance metrics, including task completion time (TCT), error rate (ER), and assistance rate (AR), will be analyzed according to normality test results. Normally distributed variables will be presented as mean ± SD, and non-normally distributed variables as median with interquartile range (IQR).

Demographic and clinical characteristics, along with eHEALS scores, will be summarized using descriptive statistics. Categorical variables will be reported as frequencies and percentages [*n* (%)], while continuous variables will be presented as mean ± SD or median (IQR), depending on the data distribution.

Qualitative data from post-test interviews will be analyzed using conventional content analysis. Two researchers will independently code the transcripts, compare and reconcile coding discrepancies through discussion, and develop categories and themes following established analytic procedures. Qualitative findings will be integrated with quantitative usability outcomes to support a comprehensive interpretation of overall usability.

## Discussion

3

The presented study protocol outlines a patient-centered WeChat-based digital health intervention for esophageal cancer patients, developed through Patient Journey Mapping (PJM) and informed by the Integrated Theory of Health Behavior Change (ITHBC).

Unlike previous mHealth interventions for cancer patients that often lack user engagement and contextual relevance (29, 57), this study incorporates PJM to systematically identify health management needs across the care continuum. This user-informed approach improves alignment with patient experiences and addresses critical gaps in existing care pathways, which may inform future refinement of digital health strategies and clinical services.

Furthermore, the mini-program has the potential to enhance patient self-management and optimize healthcare resource utilization. At the individual level, a disease-specific digital health tool may improve patients' disease awareness, strengthen self-management capabilities, and ultimately enhance their quality of life (58). Compared to previous mHealth studies, this program offers advantages in interactivity, allowing for a more personalized and adaptive user experience. At the system level, it could help reduce avoidable hospital visits and streamline care delivery, thereby potentially lowering medical costs.

Third, the mixed-method usability evaluation enhances the interpretability of findings. Quantitative metrics provide objective evidence of system performance, whereas post-test interviews help uncover contextual factors and latent user needs that cannot be captured by metrics alone. This integrated approach aligns with recommended practices for early-stage digital health evaluation and supports targeted, evidence-informed refinement of the mini-program.

This study integrates PJM and ITHBC to inform the development of a targeted digital health intervention. By grounding the design in patient needs and behavioral theory, the mini-program is expected to promote user engagement and adherence. Although tailored to EC patients, this methodological approach may provide a useful reference for developing digital health tools for other chronic disease populations.

## Limitations

4

This study has several limitations that should be acknowledged. First, the sample is drawn from a single center, which may limit the generalizability of findings to other geographic or clinical settings. Second, variations in digital literacy, particularly among older adults, may limit full engagement with the mini-program. Although eHealth literacy will be measured using the eHEALS, individuals with very low digital skills may remain under-represented. Third, the study primarily focuses on early-stage usability evaluation rather than clinical effectiveness. Future evaluations, once the prototype is stabilized, may adopt more rigorous comparative designs (e.g., randomized or cross-over trials where appropriate) and assess clinical endpoints such as quality of life, symptom control, and health-management behaviors to evaluate effectiveness and support potential scalability.

## Conclusion

5

This study develops and evaluates a WeChat-based mini-program to support personalized health management for patients with EC. The anticipated findings may enrich the evidence base for digital health interventions and offer practical insights for optimizing and scaling mHealth tools. While this study primarily focuses on usability over clinical efficacy, its methodological framework and multidimensional evaluation approach lay the groundwork for further research. Future studies should assess its impact on self-management, healthcare resource utilization, and health outcomes, as well as explore its integration and scalability in clinical practice.

## Data Availability

This manuscript reports a study protocol; no data have been collected or analyzed at this stage. In accordance with the FAIR Guiding Principles (59), any data generated during the study will be securely stored on institutional servers and made findable and accessible to authorized researchers upon reasonable request. Data will be documented in a standardized format to ensure interoperability and enable reuse in future research, while maintaining participant confidentiality and ethical considerations.
